### **6.2 Stabilization Initiation Visit 2 (Day -14)**

Eligible subjects will return to the clinic in the morning for the following.

1. Review of medical history and concomitant therapies and current health status
2. Receive paper diaries for recording study product use, changes in concomitant therapies, physical activities, and any side effects/changes in current conditions will be recorded by the subject in this diary.

Protocol 15NRHC: A randomized, double-blind, placebo controlled parallel study investigating the effects of Niagen™ (Nicotinamide Riboside) on Niagen™ metabolites in healthy adults

3. Receive 3-Day-Food records, which will be used to record all food and beverages consumed on two weekdays and one weekend day every week.
4. Receive dietary counselling from a dietician for the dietary restrictions for the study. These restrictions include:
  - a. Avoiding foods containing high amounts of tryptophan and niacin;
  - b. Limiting exposure to food containing moderate amounts of tryptophan and niacin;
  - c. Avoiding foods and beverages known to contain NR during specified periods of time prior to and during the study. A list of these foods and beverages are provided below:
    - i. Vitamins and health supplements containing niacin (nicotinic acid) or nicotinamide for 14 days prior to enrolment and during the study
    - ii. Nutritional yeast (14 days prior to enrolment, during the study)
    - iii. Whey proteins (14 days prior to enrolment, during the study)
    - iv. Energy drinks (14 days prior to enrolment, during the study)

See Appendix 2 for a detailed list of food to avoid/limit

Study staff will be in contact with the subject weekly to facilitate dietary compliance.

5. The next visit will be scheduled after 14 days.

### 6.3 Visit 3 – Baseline (Day 0)

Eligible participants will return to the clinic in the morning, after fasting for 12 hours (nothing to eat or drink except water) for baseline assessments. Participants must not have consumed caffeine or exercised on the day of the visit, prior to the visit.

1. Review of medical history and concomitant therapies and current health status
2. A physical exam will be conducted
3. Participants will be randomized into the study.
4. Participants will be weighed and BMI will be calculated
5. Resting blood pressure and heart rate will be measured
6. REE will be evaluated
7. Study diaries and 3-Day Food Records will be collected and reviewed. Subjects will receive dietary counselling from a dietician.
8. Collect pre-dose urine sample for the measurement of Niagen™ metabolites and random urine creatinine analysis
9. Collect pre-dose blood for measurement of Niagen™ metabolite
10. Collect pre-dose blood samples for lipid panel, amino acid panel, hsCRP, AST, ALT, GGT and BUN
11. Collect muscle biopsy from the *Vastus Lateralis* of subject's leg for Niagen™ metabolite analyses.
12. New study diaries and 3-Day Food records will be dispensed to the participant. 3-Day Food records will be completed every week until the next visit, and the study diary will be completed daily.
13. Investigational product will be dispensed according to the randomization schedule.
14. After all assessments are completed the participant will take the first dose (4 capsules) of the product at the clinic.
15. Participants will be instructed in detail by site personnel about the treatment regimen.
16. The next visit will be scheduled for Day 7 this visit ( $\pm$  3 days).

Protocol 15NRHC: A randomized, double-blind, placebo controlled parallel study investigating the effects of Niagen™ (Nicotinamide Riboside) on Niagen™ metabolites in healthy adults

Study staff will be in contact with the subject weekly to facilitate dietary compliance.

#### **6.4 Visit 4 and 5 (Days 7 and 14 ± 3 days)**

Subjects will return to the clinic after fasting for 12 hours (nothing to eat or drink except water). Participants must not have consumed caffeine or exercised on the day of the visit, prior to the visit.

1. Review of medical history and concomitant therapies, current health status and adverse events
2. Unused investigational product in the original packaging and the remnants of the used packages will be collected and compliance will be calculated by counting the returned unused product.
3. Study diaries and 3-Day Food Records will be collected and reviewed.
4. New study diaries and 3- day food records will be dispensed. 3-Day Food records will be completed every week until the next visit, and study diaries will be completed daily until the next visit. Subjects will receive dietary counselling from a dietician.
5. Participant will be weighed and BMI will be calculated
6. Resting blood pressure and heart rate will be measured
7. REE will be evaluated
8. Collect blood for Niagen™ metabolite analysis
9. Collect urine for Niagen™ metabolite and random urine creatinine analyses
10. Collect blood samples for lipid panel, amino acid panel, hsCRP, AST, ALT, GGT and BUN
11. The next visit will be scheduled at the same time of day as previous visits (± 3 days).

Study staff will be in contact with the subject weekly to facilitate dietary compliance.

#### **6.5 Visit 6 (Day 28 ± 3 days)**

Subjects will return to the clinic after fasting for 12 hours (nothing to eat or drink except water). Participants must not have consumed caffeine or exercised on the day of the visit, prior to the visit.

1. Review of medical history and concomitant therapies, current health status and adverse events
2. Unused investigational product in the original packaging and the remnants of the used packages will be collected and compliance will be calculated by counting the returned unused product.
3. Study diaries and 3-Day Food Records will be collected and reviewed.
4. New study diaries and 3- day food records will be dispensed. 3-Day Food records will be completed every week until the next visit, and study diaries will be completed daily until the next visit. Subjects will receive dietary counselling from a dietician.
5. Participant will be weighed and BMI will be calculated
6. Resting blood pressure and heart rate will be measured
7. REE will be evaluated
8. Collect blood for Niagen™ metabolite analysis

Protocol 15NRHC: A randomized, double-blind, placebo controlled parallel study investigating the effects of Niagen™ (Nicotinamide Riboside) on Niagen™ metabolites in healthy adults

9. Collect urine for Niagen™ metabolite and random urine creatinine analyses.
10. Collect blood samples for lipid panel, amino acid panel, CBC, electrolytes (Na, K, Cl), HbA1c, creatinine, bilirubin, hsCRP, AST, ALT, GGT and BUN
11. The next visit will be scheduled at the same time of day as previous visits ( $\pm 3$  days).

Study staff will be in contact with the subject weekly to facilitate dietary compliance.

## **6.6 Visit 7- End of Study (Day 56 $\pm$ 3 days)**

Subjects will return to the clinic after fasting for 12 hours (nothing to eat or drink except water). Participants must not have consumed caffeine or exercised on the day of the visit, prior to the visit.

1. Review of medical history and concomitant therapies, current health status and adverse events
2. Unused investigational product in the original packaging and the remnants of the used packages will be collected and compliance will be calculated by counting the returned unused product.
3. Study diaries and 3-Day Food records will be collected and reviewed
4. Subjects will be weighed and BMI will be calculated
5. Resting blood pressure and heart rate will be calculated
6. REE will be evaluated
7. Collect blood for Niagen™ metabolite analysis
8. Collect Urine for Niagen™ metabolite and random urine creatinine analyses
9. A muscle biopsy will be taken from the *Vastus Lateralis* of subjects leg for NAD metabolite analyses
10. Collect blood samples for lipid panel, amino acid panel, hsCRP, CBC, electrolytes (Na, K, Cl), HbA1c, creatinine, AST, ALT, GGT, BUN and bilirubin

## **6.7 Clinical Assessments and Procedures**

Calculations or measurements of specific parameters are required as indicated in the schedule of assessments. Instructions for determining these parameters are provided in the following sections.

### **6.7.1 Height, Weight**

Weight measurements should be performed with shoes removed, and bladder empty. Subjects should be weighed on the same scale at all visits.

At least two separate measurements should be taken at each visit. If the two measurements are more than 0.5 kg (1.1 lbs) apart, a third measurement should be taken. Then the two closest values are going to be selected and entered in the database.

Measurement of height should be performed with the subject's shoes removed. The subject's knees should be straightened, and head held upright.

Protocol 15NRHC: A randomized, double-blind, placebo controlled parallel study investigating the effects of Niagen™ (Nicotinamide Riboside) on Niagen™ metabolites in healthy adults

### 6.7.2 Blood Pressure

In office, seated resting blood pressure and heart rate will be determined from 3 measurements obtained at least 1 minute apart. One arm will be chosen and used consistently throughout the study. Blood pressure will be checked in both arms at the first examination. If a consistent inter-arm difference exists, the arm with the higher pressure will be used throughout the study. The arm selected for use at the initial visit will be documented in the study file.

The subject should be seated comfortably with the back supported and the upper arm bared without restrictive clothing. Feet should be flat on the floor, legs should not be crossed. The subject should rest in this position for at least 5 minutes prior to the first reading.

The same recording method and the same equipment should be used for each subject throughout the study.

### 6.7.3 Micro-Needle Muscle Biopsy

Micro-needle muscle biopsies will be performed once at the Baseline visit (Visit 3, Day 0) once at the End of Study Visit (Visit 7, Day 56). Prior to the procedure, the Qualified Investigator, or designate, will ensure that the subject has completed the Muscle Biopsy Screening Form and has read and signed the Muscle Biopsy Information Sheet and fully understands the nature of the procedure and any associated risks.

The biopsy samples will be taken from the *Vastus Lateralis* muscle by an experienced physician or trained delegate. The surface area where the micro-needle will be inserted will be disinfected and anesthetized using a local anesthetic. A cannula will be used to pierce the skin and a micro-needle will be inserted. Following collection of the muscle sample, the needle will be removed and pressure will be applied to the area where the needle was inserted for a few minutes until any bleeding stops. The wound will then be treated and bandaged appropriately.

### 6.7.4 Indirect Calorimeter Analysis

Resting energy expenditure (REE, or resting metabolic rate; RMR) will be calculated at baseline and all subsequent visits to the clinic, until study completion. Subjects will come into the clinic having fasted for 12 hours and having avoided exercising and consuming caffeine on the day of testing, prior to the test. Subjects will be asked to place the ReeVue MetaBreather hose in their mouth and breathe normally. Participants will have nose clips placed on their nose for the duration of the analysis, which completes after ~10min. Subject REE data will be printed from the ReeVue machine and stored for further analysis.

### 6.7.5 Compliance

Investigational product compliance calculations will be necessary in this study because the products will be consumed at home. Subjects will be asked to bring any unused packages, the remains of the used packages, and their diaries to each study visit.

Compliance will be assessed by counting the returned unused study product at each visit. Compliance is calculated by determining the number of dosage units taken divided by the number of dosage units expected to have been taken multiplied by 100.

$$\frac{\text{number of dosage units taken}}{\text{number of dosage units expected to have been taken}} \times 100\%$$

In the event of a discrepancy between the information in the subject diary and the amount of study product returned, use will be based on the product returned unless an explanation for loss of

Protocol 15NRHC: A randomized, double-blind, placebo controlled parallel study investigating the effects of Niagen™ (Nicotinamide Riboside) on Niagen™ metabolites in healthy adults

product has been provided. Subjects found to have a compliance of <80% or >120% will be counseled. A compliance of <70% or >130% will be considered as non-compliant and any subject demonstrating non-compliance for two consecutive visits will be withdrawn from the study.

Compliance to the protocol will also be assessed by reviewing the diaries completed by each subject for adherence to the study's dietary restrictions, ingestion of the investigational product, and maintenance of physical activity levels, and the determination of the urine Niagen™ metabolites.

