##### **Removal by PI:**

Participant discontinuation should be considered at the discretion of the Qualified Investigator. The circumstances of any discontinuation have to be documented in detail in the participant file and final report. If possible, the evaluations planned for the end of treatment will be carried out at the time when the participant is withdrawn from the study. A participant leaving the study prematurely will NOT be replaced by another. It is understood by all concerned that an excessive rate of withdrawals can render the study un-interpretable; therefore, unnecessary withdrawal of participants should be avoided.

Criteria for removal of participants from the study will include:

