### **Protocol violation**

Any participant found to have entered this study in violation of the protocol will be discontinued from the study at the discretion of the Qualified Investigator. This will include any participant found to have been inappropriately enrolled (did not meet eligibility criteria). Participant non-compliance includes not showing up for study visits, not taking the investigational product as directed, or refusing to undergo study visit procedures. Participants who are found to be taking prohibited medications or supplements without the knowledge of the Qualified Investigator will also be withdrawn. Any major protocol deviations (i.e., those that increase the risk to participants and/or compromise the integrity of the study or its results) will result in participant discontinuation.

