#### **7.2.2 Treatment and Follow-up of Laboratory Abnormalities**

In the event of subject-initiated withdrawal or clinically significant unexplained abnormal laboratory test values, the subject will be withdrawn from the treatment and will remain in the study and be required to attend all remaining study visits as part of a safety arm.

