#### **8.2 Analysis Plan**

- The **Safety Population** will consist of all subjects who received any amount of either product, and on whom any post-randomization safety information is available.

Protocol 15NRHC: A randomized, double-blind, placebo controlled parallel study investigating the effects of Niagen™ (Nicotinamide Riboside) on Niagen™ metabolites in healthy adults

- The **Intent-to-Treat (ITT) Population** consists of all subjects who received either product, and on whom any post-randomization efficacy information is available.
- The **Per Protocol (PP) Population** "Per Protocol (PP) Population" consists of all subjects who consumed at least 80% of treatment or placebo doses do not have any major protocol violations and complete all study visits and procedures connected with measurement of the primary variable.

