### 8.3 Analysis Plan

An effectiveness analysis based on the modified intent-to-treat population and an efficacy analysis based on the per protocol population will be performed. Variables will be tested for normality and log-normality. Log-normally distributed variables will be analyzed in the logarithmic domain. Non-normal variables will be analyzed by appropriate non-parametric tests.

All missing values in the intent-to-treat (effectiveness) analysis will be imputed with the most recent previously-available value (LOCF, or "last-observation-carried-forward" imputation). No imputation will be performed for missing values of safety variables.

For each numerical endpoint, a summary table will be prepared with a variety of summary statistics including mean, standard deviation, median, minimum value, and maximum value for each time point-treatment pairing. In order to account for any a priori differences between groups, the summary statistics of the changes from baseline will also be provided. For parameters requiring the logarithmic transformation, the summary statistics will be provided as non-transformed values. Mean values will be displayed as graphs, with a separate line for each product, and error bars indicating  $\pm 1$  SEM. Mean changes from baseline will be graphed similarly.

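### Section 6.7.5 withdraws repeated non-compliers from the study rather than from product alone, so Day 56 samples that could have been taken are lost and filled by LOCF

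*Protocol*

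**What the plan says.** Section 6.7.5 (Compliance) counts returned product at each visit. Subjects outside 80% to 120% are counselled. Those below 70% or above 130% are non-compliant, and "any subject demonstrating non-compliance for two consecutive visits will be withdrawn from the study". The exit is from the study, and the wording is mandatory.

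Related provisions in the protocol:

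- Section 4.4, Protocol violation: "Participant non-compliance includes not showing up for study visits, not taking the investigational product as directed". Non-adherence therefore also stands among the removal criteria there, and the same paragraph makes discontinuation follow any major deviation.
- Section 4.4, Removal by PI: "If possible, the evaluations planned for the end of treatment will be carried out at the time when the participant is withdrawn"; and "A participant leaving the study prematurely will NOT be replaced by another".
- Section 7.2.2: subjects who withdraw themselves, or who have clinically significant unexplained laboratory values, come off treatment but "will remain in the study and be required to attend all remaining study visits as part of a safety arm".
- Section 8.2: the ITT population "consists of all subjects who received either product, and on whom any post-randomization efficacy information is available". The Per Protocol population "consists of all subjects who consumed at least 80% of treatment or placebo doses", with no major violations and with all visits tied to the primary variable completed.
- Section 8.3: "All missing values in the intent-to-treat (effectiveness) analysis will be imputed with the most recent previously-available value".
- Section 6.7.3: biopsies are planned at Day 0 and Day 56 only.

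**The concern.** The primary outcome is a randomized comparison with placebo after 8 weeks. A subject removed at Day 14 or Day 28 has no Day 56 value, yet remains in ITT and is not replaced. The value analysed in its place comes from the exit visit. For muscle it comes from baseline if no exit biopsy is taken, which amounts to recording no change.

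Whether a value is missing then depends on what the subject did after randomization, and this may differ between arms. Another missing-data method in the statistical analysis plan would alter the imputation but could not restore the observation. The subjects concerned are attending a clinic where the samples are already scheduled.

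**Working it through.** **When the rule can fire.** Compliance is counted at Visits 4 to 7 (Days 7, 14, 28, 56). Two consecutive failures end at Visit 5, 6 or 7. If the second failure is at Visit 7, nothing is lost. The rule costs data when Visit 5 fails together with Visit 4 or Visit 6.

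**Missed doses needed for compliance below 70%.**
- 3 of 7 missed leaves 57.1%; 5 of 14 missed leaves 64.3%.
- At nominal days: 3 + 3 = 6 missed doses by Day 14, or 3 + 5 = 8 between Day 7 and Day 28.
- Within the ±3-day windows, 4 can be enough. With Visit 4 on Day 6 and Visit 5 on Day 12, 2 of 6 missed each time leaves 66.7%.
- Above 130% over 7 days needs 10 daily doses (143%).

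**The plan's own figure (section 8.1).** SD 3.1, baseline-to-end correlation 0.5, effect 2.5 µM/mM creatinine, two-sided 0.05 (sidedness assumed), 80% power.
- SD of change = 3.1 × √(2(1 − 0.5)) = 3.1.
- n = 2 × 3.1² × (1.960 + 0.842)² / 2.5² = 24.1, so 25 per arm.
- 25/0.8 = 31.25, so 32; × 4 = 128, as stated.
- With 35 per arm, the standard error of an arm difference is 3.1 × √(2/35) = 0.741, and t-test power for 2.5 is 91.4%.

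**How often (assumed; the protocol gives no miss rate).** Removals before Day 56 per arm of 35, at average miss rates of 10% and 20%:

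| Model | 10% | 20% |
|---|---|---|
| Independent misses, common rate | 0.03 | 1.34 |
| Person-specific Beta rates, concentration 5 | 1.9 | 5.5 |
| Person-specific Beta rates, concentration 2 | 3.0 | 6.9 |

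The count runs from almost none to about seven, so it cannot be pinned down.

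**Expected LOCF error.** Assume the urinary effect is proportional to intake. In the Beta models, those removed took about 39% to 50% of doses over Days 0–14 and would have taken about 43% to 59% over Days 28–56. Shift in the arm mean = 2.5 × (later − earlier intake) × removals/35:
- 3.0 removals, 41% then 46%: 2.5 × 0.05 × 3.0/35 = 0.011.
- 6.9 removals, 39% then 43%: 2.5 × 0.04 × 6.9/35 = 0.020.
- 1.9 removals, 50% then 59%: 2.5 × 0.09 × 1.9/35 = 0.012.
- 5.5 removals, 48% then 55%: 2.5 × 0.07 × 5.5/35 = 0.028.

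That is about 0.01 to 0.03, around 1% of 2.5 or less.

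**Extreme cases.** The rule covers any intake below 70%, including zero.
- Zero carried intake, full recovery had the person stayed: 3 removals give 2.5 × 3/35 = 0.214 too low (8.6% of target, 0.29 SE, power 86.0%). 6.9 removals give 2.5 × 6.9/35 = 0.493 too low (20%, 0.67 SE, power 76%).
- Carried intake just under 70%, then a complete stop: 2.5 × 0.7 × 3/35 = 0.15 too high, or 2.5 × 0.7 × 6.9/35 = 0.345 too high.

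**Muscle.** Three removals without an exit biopsy set 3/35 = 8.6% of an arm to no change.

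**Does the Per Protocol definition already catch these people?** Not once they stay. Six misses followed by full intake is 50/56 = 89%, and eight misses is 48/56 = 86%. Both pass the 80% dose criterion, which also has no upper limit.

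**The case against.** The strongest reply is that this is a deliberate policy with little consequence. Sections 4.4 and 6.7.5 agree that non-adherers leave. Section 4.4 gives the investigator discretion and warns against unnecessary withdrawals. It also asks for end-of-treatment evaluations at exit, which would include the biopsy. The sample size allows 20% attrition, and ITT and per-protocol analyses are both planned. The rule also removes over-users and spares non-adherent volunteers a second biopsy.

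Much of this stands. It is a design choice and not a slip, and the expected effect on the primary endpoint is small. It does not remove the point. The specific mandatory wording of 6.7.5 most naturally governs over the general discretion. An exit evaluation is conditional and is not a Day 56 value. An attrition allowance protects sample size but not comparability.

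Three stronger readings are tempting:

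- *That 6.7.5 contradicts 7.2.2.* It does not. The triggers differ, and 7.2.2 keeps subjects as a safety arm without saying that efficacy samples continue. It shows only that off-treatment attendance is accepted in this trial.
- *That the primary result is materially biased or the trial underpowered.* The protocol gives no frequency or direction, and the illustrative models give an expected error near zero.
- *That the shift is at most about 5% of target.* That follows from three removals with carried intake fixed at 8 of 14 doses: 2.5 × (8/14) × 3/35 = 0.122. The rule sets no such floor on intake, so this is not a bound.

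**Conclusion.** The point holds as a cheap improvement. Section 6.7.5 creates avoidable missing Day 56 data that depend on behaviour after randomization, and analysis cannot repair the loss. Frequency and direction of bias are not determinable from the protocol: LOCF understates the effect if intake would have recovered and overstates it if the person would have stopped.

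The expected primary-endpoint error is about 0.01 to 0.03 µM/mM, given proportional effect and persistent person-specific adherence. The extreme understatement is 0.21 to 0.49 µM/mM against the 2.5 target, given 3 to 6.9 removals in one active arm, zero carried intake and full later recovery. All removal counts are assumptions. Muscle is most exposed, and only where no exit biopsy is obtained.

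**What to change.** Three short text changes:

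- **Section 6.7.5.** Replace withdrawal from the study with: a subject who is non-compliant at two consecutive visits is counselled again (below 70%) or has product stopped (above 130%), and stays in the study for every remaining visit. Day 56 urine and blood, and muscle where the subject agrees, are collected and used in the ITT analysis.
- **Section 4.4, Protocol violation.** State that non-compliance with product intake, including when classed as a major deviation, is handled under 6.7.5 and is not by itself a reason for discontinuation from the study. Without this, the major-deviation sentence could still force removal.
- **Section 8.2.** Add to the Per Protocol definition that subjects below 70% or above 130% at two consecutive visits are excluded.

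The other removal criteria and the subject's right to leave are unchanged. The visits and biopsies are already planned for all 35 per arm. The cost is slight dilution of the ITT effect by poor adherers, and some second biopsies taken from, or declined by, non-adherent volunteers.
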